### Data collection instruments

The data collection instrument developed specifically for this study was submitted to content validation by eight experts with a doctorate and relevant experience in Breastfeeding Counseling, teaching, and evidence-based research.

The baseline instrument contains three parts, namely: Part I—sociodemographic variables: age; self-declared race marital status, and, if living with a partner, age, and level of education; schooling, family income, occupation, maternity leave, paternity leave, origin and presence of a companion at the time of the interview; Part II—clinical variables: smoking, coffee drinking, health problems, and medication use; Part III—obstetric variables: prenatal care and the number of consultations; guidance on breastfeeding during prenatal care and sources, including specification in case of professional guidance. Information about the delivery/birth will be collected, such as date of delivery, type of delivery, if the puerperal woman had a companion during labor and delivery; if there was early contact with the newborn, and if the mother started breastfeeding in the first hour of life. About the NB, weight, height, gestational age, and type of breastfeeding data will be collected at the time of hospital discharge.

The information will be collected through interviews and medical records.

Women allocated to the intervention group will be encouraged to answer the following open questions: How are you breastfeeding? Moreover, if she has doubts or concerns, they will be explored with: Tell me about it… Next, the following guiding question will be used: How are you feeling breastfeeding? Furthermore, in the end, you will be asked: What led you to breastfeed? The validated protocol for counseling on breastfeeding during hospitalization in rooming-in wards will be used for all responses.

For evaluation based on observation of breastfeeding, the LACTH [24] scale will be used—attachment, swallowing, type of nipple, comfort, and positioning, applied to both groups, based on observation of at least one breastfeeding.

A nipple-areolar evaluation will be performed, regarding skin color and type of nipple [27]. In case of nipple-areolar lesions detected by visual inspection, the Nipple-Areolar Lesions Classification Instrument [28] and the Nipple Trauma Score [29] will be applied.

The presence of breast or nipple pain will also be evaluated based on applying the Visual Analog Pain Scale [30, 31], and, in the case of pain, pain characteristics [32]. At the end of the interview, women from both groups will be invited to watch the videoscribe produced.

The researcher will record the scale items adapted from the observation and evaluation form for the rooming-in wards—Fantinelli’s scale, which allows for assessing the care complexity of the dyad [25].

In the first and second weeks of the newborn’s life, as well as in the first, fourth, and sixth months, three attempts to contact the postpartum woman by telephone will be made from the number provided in the initial contact, at different times, and at least one attempt to contact with familiar.

In the first and second weeks, data on the type of breastfeeding at the time will be collected; introduction of artificial milk, nipple-areolar lesions or pain, breast engorgement, use of pacifiers, professional search/support for breastfeeding issues, weaning, follow-up of childcare, and neonatal intercurrences. Interventions will not be applied to both groups.

From the first month, the Edinburgh Postpartum Depression Scale will be applied [33, 34]. Hospitalizations and childhood illnesses will also be questioned at 2, 4, and 6 months of the child’s life. The same questionnaire will be used for the following months until the conclusion of the protocol in the sixth month.

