## Methods

This clinical trial has the following specific objectives:Compare the percentage of occurrence of nipple-areolar lesions in the first and second weeks of life for the intervention and control groups;Compare breast complications in the first 2 weeks based on mother reports and compare results between groups;Compare the percentage of exclusive breastfeeding in the first, fourth, and sixth month in both groups;Evaluate postpartum depression scores at different times (1, 4, and 6 months) and compare the occurrence between the two groups;Compare the rate of hospitalizations and occurrence of childhood illnesses at 2, 4, and 6 months of life, according to the type of breastfeeding and between groups;Compare the percentage of weaning between groups;Evaluate the care complexity of the dyads (minimal, intermediate, semi-intensive, and intensive care) participating in the study, based on a validated scale, andPresent the performance scores of the nursing mother and the baby during breastfeeding during hospitalization in the rooming-in wards, in the two study groups, based on a validated scale (LACTH).

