After hospital discharge, telephone contacts will be made through the number provided by the participant to collect the outcomes. To ensure that there is no loss of contact, the researcher will request the contact of the postpartum woman and a family member at the time of allocation. Contact will be made by the researcher who collected the data with the postpartum women included to maintain the link with the postpartum women and reduce sample losses. Contacts will be made: in the first and second weeks of life, with 1, 4, and 6 months of the child’s life to collect the outcomes.

It should be noted that all researchers at the participating centers are not part of the care teams at the units. All were trained to intervene with the Clinical Management of Breastfeeding course (60 h) and Counseling Workshop (16 h), including practical activities, totaling 76 h of training.

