### Control group

The control group will receive standard institutional care, that is, the assistance offered by a professional, from the institution itself, without intervention by the researchers.

In these cases, the researcher responsible for data collection will conduct the interview and non-participant observation of at least one feeding without applying any intervention. The same instruments used in evaluating the intervention group will be applied. At the end of the interview, participants will also be invited to watch the videoscribe produced for the study.

Telephone contacts will be made, as well as in the intervention group, in the first and second weeks of life, with 1, 4, and 6 months of the child’s life to collect the outcomes.

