In the intervention group, the postpartum woman will be approached with the strategy of counseling, breast evaluation, and at least one breastfeeding and interview according to a validated protocol. Ultimately, the researcher will reinforce the subsequent contacts, which will succeed in the allocation, interspersed in the morning and afternoon, depending on time zero, until hospital discharge. In the follow-up at the hospital, an approach with a counseling strategy will be carried out, identifying doubts and potential needs. In the end, the videoscribe will be offered and reinforced about subsequent telephone contacts for follow-up and their importance.

To characterize the sampling, the researcher will complete a daily list of eligible postpartum women, included or not included, and reasons for non-inclusion.

If the researcher detects abnormalities in the mechanics of breastfeeding or changes in the mother–child bond, the care team members will be notified, and the participant must be excluded.

Follow-up interviews will be done through phone calls. The researcher will make three telephone contact attempts at different times of the day: between 12:30 pm and 1:30 pm, from 4:00 pm to 5:00 pm, or at another preferred time indicated by the participant. If the attempt is unsuccessful, the researcher will try to contact the number provided by the family member. If accepted, the researcher will apply the questionnaire, thank them, and inform a new contact within a week. Contact will be made by the researcher who collected the data with the postpartum women included to maintain the link with the postpartum women and reduce sample losses.

In the second week, the same procedures will be carried out, but at the end, the researcher will signal a new contact in 2 weeks; in the first month, he will inform that he will return in 3 months, and on the fourth month, he will inform that the next call will be in 2 months. At the end of the protocol, the researcher will close the research and thank the participant.

Postpartum women who are not followed up in the first 15 days, after three unsuccessful contact attempts and at least one contact with a family member at different times, will be excluded.

All data will be completed in Google Forms® electronic forms on tablets purchased for this purpose. Only researchers will have access to the electronic database, collection instruments, and consent forms.

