### Secondary outcomes

Nipple-areolar lesions: lesion(s) in the nipple-areolar region(s) with or without disruption of the skin barrier.Nipple or breast pain: verbal report of pain, describing its characteristics, associated with breastfeeding.Breast complications: occurrence of engorgement or mastitis.Exclusive breastfeeding in the first, fourth, and sixth months of life: exclusive breastfeeding in this period.Postpartum depression scores: measured by the Edinburgh Scale, indicated for tracking signs indicative of puerperal depression, which should be applied after the persistence of symptoms of puerperal blues, that is, with continuity of symptoms after 1 month and consistent with the birth.Hospitalizations and occurrence of illnesses in childhood: based on the mothers’ report to the telephone contact.Weaning: interruption of breastfeeding, considered early, when it occurs before 4 months of the child’s life.Care complexity of the dyads: classification into minimal, intermediate, semi-intensive, and intensive care, based on the care required by postpartum woman and newborn.Performance of the postpartum women and newborn during breastfeeding: based on the validated scale (LACTH) application.

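### Hospitalisation and childhood illness are to be asked about and compared at 2 months, but no follow-up call is scheduled at 2 months

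*Protocol article*

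**What the plan says.** The specific objectives at the start of Methods include: "Compare the rate of hospitalizations and occurrence of childhood illnesses at 2, 4, and 6 months of life, according to the type of breastfeeding" and also between the two groups. Data collection instruments repeats the timing as an instruction: "Hospitalizations and childhood illnesses will also be questioned at 2, 4, and 6 months". Secondary outcomes names the source: "Hospitalizations and occurrence of illnesses in childhood: based on the mothers’ report to the telephone contact".

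The call schedule is stated in several places:

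- Experimental group: "Contacts will be made: in the first and second weeks of life, with 1, 4, and 6 months".
- Control group: "in the first and second weeks of life, with 1, 4, and 6 months".
- Data collection instruments, which also carries the 2-month instruction, lists the first and second weeks, "as well as in the first, fourth, and sixth months, three attempts to contact the postpartum woman by telephone".
- Recruitment and data collection procedures gives the intervals between calls, including "in the first month, he will inform that he will return in 3 months". From month 4, the next call is announced for two months later.

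**The concern.** The outcome is collected by telephone, so a value at 2 months needs a call at 2 months or a later question about that period. The first is not in the schedule and the second is not in the article.

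The gap affects both halves of the objective. The between-group comparison lacks the events. The comparison by type of breastfeeding also lacks the feeding status at 2 months, because feeding type too is recorded only at the scheduled calls.

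Three centres work from this text. Faced with the conflict, one team might make an extra call, another might treat month 1 as the early point, and a third might ask retrospectively at month 4. The resulting 2-month data would not be comparable across centres. With recall at month 4, events would be reported long after they happened, by mothers who know their allocation.

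**Working it through.** No sample size, power or error rate is involved. The check rebuilds the call dates and sets them against the outcome dates.

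**Inputs**

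- Outcome times (Methods, specific objectives; Data collection instruments): 2, 4 and 6 months.
- Source (Secondary outcomes): the mother's report by telephone.
- Intervals between calls (Recruitment and data collection procedures): 1 week after the first call, then 2 weeks, 3 months and 2 months.

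**Calls rebuilt from the intervals**

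- First call: week 1.
- Week 1 + 1 week = week 2.
- Week 2 + 2 weeks = week 4, the month-1 call.
- Month 1 + 3 months = month 4.
- Month 4 + 2 months = month 6.

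This reproduces the list given for each arm and in Data collection instruments, so the four statements of the schedule agree with one another.

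**Outcome times against calls**

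| Planned time point | Call at that time? | Nearest calls |
|---|---|---|
| 2 months | No | month 1 (2 − 1 = 1 month before) and month 4 (4 − 2 = 2 months after) |
| 4 months | Yes | – |
| 6 months | Yes | – |

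One of three time points (1/3, or 33%) has no contact.

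**Could another statement supply the 2-month value?**

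- *Continued use of the questionnaire.* Data collection instruments says that the same questionnaire serves for the later months up to the sixth. That describes the form, not an additional call, and the stated three-month interval after month 1 leaves no room for one.
- *Early calls.* The calls in weeks 1 and 2 ask about neonatal problems. They end well before 2 months.
- *Recall at month 4.* An event at 2 months would be 4 − 2 = 2 months old when reported, and one at 1 month would be 4 − 1 = 3 months old. The article describes no such retrospective question.
- *Figures 3 and 4.* The follow-up flowchart and the SPIRIT schedule are not reproduced in the text at hand. A 2-month contact shown there would contradict the schedule in the text, so reconciliation would still be needed.

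**The case against.** The strongest reply is that this is probably a slip on a minor item. Exclusive breastfeeding and the depression score are set at 1, 4 and 6 months, so the 2 may simply stand for 1. The 4- and 6-month comparisons match existing calls, and the primary outcome, duration of exclusive breastfeeding, does not depend on this item. All of that stands and limits the weight of the point. It does not remove it: the 2 appears in both the objective and the collection instruction, and nothing in the article shows which was meant.

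A reader might infer that the 2-month comparison cannot be made at all. The documents do not support that. The outcome is maternal report, and dated events could be asked about at month 4. What can be said is that no contact is scheduled then and no recall is planned.

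A reader might also infer that the reference periods at months 4 and 6 are unclear, so that events may be missed or counted twice. That is not supported either. The collection instrument exists and was content-validated by eight experts, but its items are not reproduced, and a journal article commonly leaves such wording to the full protocol.

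Finally, the figure of one in three only counts time points within one of several secondary outcomes. It does not measure bias or lost precision.

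**Conclusion.** The point holds as a contradiction between two stated rules. Hospitalisation and childhood illness are to be asked about and compared at 2, 4 and 6 months, while every statement of the schedule places the calls at weeks 1 and 2 and months 1, 4 and 6. As written, one of three planned time points for this secondary outcome has no scheduled source, either for the events or for feeding type, in either arm. This is not detail left to a fuller document, because the article fixes both the time points and the calls.

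The conclusion assumes that telephone contact is the only source for this outcome, as Secondary outcomes states, and that the figures not shown do not replace the schedule in the text. It should be corrected, but it does not threaten the trial's main result.

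**What to change.** Reconcile the sections in one of two ways.

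1. **Align the outcome with the existing calls (cheapest).** Change the time points for hospitalisation and childhood illness from 2, 4 and 6 months to 1, 4 and 6 months, both in the specific objectives and in Data collection instruments. At each of these calls, ask about events since the question was last asked: birth to month 1, month 1 to 4, and month 4 to 6. Keep both comparisons in the objective, between groups and by type of breastfeeding. No new analysis is needed to resolve the conflict.

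2. **Add the call, if a 2-month point was intended.** Insert a 2-month contact in Experimental group, Control group, Data collection instruments, and Recruitment and data collection procedures. Revise the interval announced at month 1, and record feeding type at the new call.

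Under either option, check Figures 3 and 4 against the corrected text.

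The first option costs a few more questions at a call already made, and the second an additional call per participant. Both need a protocol amendment, which Ethical aspects requires to be notified to the ethics committee, the registry and the journal. Clinical trial status says that pilot recruitment began on March 1, 2023, so it should also be recorded when pilot participants were actually asked about these events.

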### Recruitment and data collection procedures

The researcher, daily, will go to the nurses responsible for the ward and locate the census of hospitalized puerperal women and identify the primiparous women who delivered at term and the bed in which they are hospitalized. The following information will be checked in the medical records: HIV and HTLV 1 and 2 serological test results; information on neoplastic diseases currently being treated with chemotherapy; neonatal malformations; diagnosis of neonatal ankyloglossia; description of separation at birth (hospitalization in critical units—women or newborn); readmission due to maternal or neonatal complications; illicit drug users; postpartum women with a medical diagnosis of intellectual difficulty or sensory deficit. If it has any of the present criteria, it will not be included in the list for randomization. If there are no criteria for non-inclusion, randomization will be performed. The gestational age and birth weight of neonates will also be checked.

Once the criteria are met, the researcher will go to the ward, explain the study’s objectives to the selected postpartum women and read the Informed Consent Form (ICF). When deciding positively to participate, the postpartum woman must sign the ICF in two copies, receiving a copy and another that the researchers will keep. The researcher will contact the randomization center, and eligible postpartum women will be randomized to the control or intervention group as directed by the center.

In the control group, the interview, evaluation of the breasts, and at least one feeding will be performed using the abovementioned instruments. At the end (zero time), the researcher will reinforce the telephone contacts and offer the videoscribe visualization. Unfilled information can be extracted from the medical records, and the care complexity scale will be filled in.

In the intervention group, the postpartum woman will be approached with the strategy of counseling, breast evaluation, and at least one breastfeeding and interview according to a validated protocol. Ultimately, the researcher will reinforce the subsequent contacts, which will succeed in the allocation, interspersed in the morning and afternoon, depending on time zero, until hospital discharge. In the follow-up at the hospital, an approach with a counseling strategy will be carried out, identifying doubts and potential needs. In the end, the videoscribe will be offered and reinforced about subsequent telephone contacts for follow-up and their importance.

To characterize the sampling, the researcher will complete a daily list of eligible postpartum women, included or not included, and reasons for non-inclusion.

If the researcher detects abnormalities in the mechanics of breastfeeding or changes in the mother–child bond, the care team members will be notified, and the participant must be excluded.

Follow-up interviews will be done through phone calls. The researcher will make three telephone contact attempts at different times of the day: between 12:30 pm and 1:30 pm, from 4:00 pm to 5:00 pm, or at another preferred time indicated by the participant. If the attempt is unsuccessful, the researcher will try to contact the number provided by the family member. If accepted, the researcher will apply the questionnaire, thank them, and inform a new contact within a week. Contact will be made by the researcher who collected the data with the postpartum women included to maintain the link with the postpartum women and reduce sample losses.

In the second week, the same procedures will be carried out, but at the end, the researcher will signal a new contact in 2 weeks; in the first month, he will inform that he will return in 3 months, and on the fourth month, he will inform that the next call will be in 2 months. At the end of the protocol, the researcher will close the research and thank the participant.

Postpartum women who are not followed up in the first 15 days, after three unsuccessful contact attempts and at least one contact with a family member at different times, will be excluded.

All data will be completed in Google Forms® electronic forms on tablets purchased for this purpose. Only researchers will have access to the electronic database, collection instruments, and consent forms.

The flowchart for the inclusion of research participants is shown in Fig. 1, the randomization and data collection procedure and data steps are summarized in Fig. 2, and the follow-up after hospital discharge is described in Fig. 3. The flowchart for the research participants is shown in Fig. 4.

**Fig. 1 Fig1:**
[figure not shown]
Flowchart for inclusion of participants in the study

**Fig. 2 Fig2:**
[figure not shown]
Randomization flowchart and collection procedures for control and intervention groups

**Fig. 3 Fig3:**
[figure not shown]
Follow-up flowchart for the control and intervention groups after hospital discharge

**Fig. 4 Fig4:**
[figure not shown]
Standard Protocol Items: Recommendations for Interventional Trials (SPIRIT) flowchart

### Safety protocols

All biosecurity protocols will be strictly followed, and the data collection team will use all necessary personal protective equipment.

As for adverse events, their occurrence is not predictable in this research, given the nature of the intervention. However, in case of any complication or adverse event for the participants, the information will be registered, and the Research Ethics Committee will be immediately communicated.

It should be noted that the study will be stopped if there is definitive evidence, during its conduction, of the benefit or absence of benefit from the intervention, which the specific Monitoring Committee will evaluate for this randomized clinical trial.

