### Experimental group

In the intervention group, counseling will be carried out by a team of nurses qualified for breastfeeding management and counseling.

Women will be encouraged to answer the following open questions: How are you breastfeeding? Moreover, if she has doubts or concerns, they will be explored with: Tell me about it… Next, the following guiding question will be used: How are you feeling breastfeeding? Furthermore, in the end, you will be asked: What led you to breastfeed? The validated protocol for counseling on breastfeeding during hospitalization in rooming-in wards will be used for all responses.

Postpartum women allocated to this group will be approached using counseling, as described above. The researcher will collect the history of breastfeeding with the counseling approach and observe the breastfeeding. During breastfeeding, the LATCH [24] scale items will be observed—latching on, swallowing, type of nipple, comfort, and positioning. Afterward, the researcher will interview the puerperal woman and fill in sociodemographic, clinical, and obstetric data.

At the end of the first counseling session, the researcher will fill in the items of the scale adapted from the observation and evaluation form for rooming-in wards—Fantinelli’s scale [25], which measures the care complexity of the dyad.

Counseling will be offered twice a day until hospital discharge in the morning and afternoon, and the start and end times of the intervention will be recorded to determine the duration.

At the end of the intervention, the women will be invited to watch a videoscribe with the theme “Breastfeeding is better,” produced by the study group, in which the advantages of breastfeeding for the mother and newborn are discussed and guidance is given to seek help in case of breast complications. The video has three distinct versions, with the voices of the researchers of each center and a version in Brazilian Sign Language. The version adapted to the participant’s location will be used. The Brazilian Sign Language version was created for inclusion and health education purposes for these women but will not be used in this study.

The intervention (implementing individualized counseling on the duration of exclusive breastfeeding) will not require alteration to usual care pathways, including use of any medication for postpartum woman or neonates and these will continue for both trial arms.

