### Criteria for discontinuing the intervention

Interim analyses will be performed every 60 days during data collection and presented to a clinical trial safety monitoring committee to assess the continuity of data collection, given the findings of adverse events or statistical differences between the groups surveyed concerning primary and secondary outcomes. The data analysis will be of the type by the finalization of the protocol, denominated explanatory.

This committee is highly recommended for RCTs being utilized by the FDA and NIH. It is suggested that in its minimum composition, it has a specialist in the subject, a specialist in RCT, a specialist in statistics/epidemiological studies, a representative of the Ethics Committee, and a representative of the users (who are in the same condition as the study participants) [26]. The proposed committee for this study will consist of five representatives, two specialists in the subject and in conducting RCTs, one specialist in epidemiological studies and statistics, a representative of the Ethics Committee, and a representative of the users. The participants of this committee will not be involved in the study team and have indicated that they are aware of this condition.

The study must be stopped if there is definitive evidence, during its conduction, of the benefit or lack of benefit of the intervention, which the specific Monitoring Committee will evaluate for this randomized clinical trial [26].

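### Between zero time and discharge the study team directly observes only the counselling arm, so in-hospital adverse events compared by arm for the monitoring committee are at risk of differential detection

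*Protocol article*

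**What the plan says.** All references are to the protocol article.

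- **Counselling arm in hospital.** Experimental group: "Counseling will be offered twice a day until hospital discharge in the morning and afternoon". Recruitment and data collection procedures describes the later contacts as "interspersed in the morning and afternoon, depending on time zero, until hospital discharge", and gives their purpose as finding out the woman's doubts and needs.
- **Control arm in hospital.** Control group: "the researcher responsible for data collection will conduct the interview and non-participant observation of at least one feeding without applying any intervention". Recruitment and data collection procedures: "In the control group, the interview, evaluation of the breasts, and at least one feeding will be performed using the abovementioned instruments". It continues: "At the end (zero time), the researcher will reinforce the telephone contacts and offer the videoscribe visualization". The next study contact described is the first-week telephone call.
- **Who the researchers are.** The section on the experimental group states that they do not belong to the units' care teams.
- **Adverse events.** Safety protocols: "in case of any complication or adverse event for the participants, the information will be registered", with immediate notice to the ethics committee.
- **Use of the data.** Criteria for discontinuing the intervention: analyses every 60 days go to the monitoring committee to assess continuation, "given the findings of adverse events or statistical differences between the groups surveyed concerning primary and secondary outcomes".
- **Discharge item.** Data collection instruments lists, for the newborn, that "type of breastfeeding data will be collected at the time of hospital discharge", with no distinction between arms.
- **After discharge.** Both arms receive the same calls at weeks 1 and 2 and months 1, 4 and 6. The week-1 and week-2 calls ask about lesions, pain, engorgement and neonatal problems.

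**The concern.** Events are registered when someone on the study team learns of them, and the opportunity to learn of them differs by arm for part of the hospital stay. A complication that arises after zero time and before discharge can be seen directly by a study nurse if the woman is being counselled. If she is a control, it reaches the study only through the medical record or a later call.

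This matters because adverse events are a stated ground for the committee's decision on continuing. With equal true risk, a by-arm table fed by spontaneous notice could show an excess in the counselling arm that reflects only the number of visits. Analysis cannot repair this afterwards if comparable control data were never collected.

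**Working it through.** The plan gives no sample size, event rate, length of stay or harm figure on this point, so there is no stated figure to reproduce. The check compares the contact schedules and then illustrates the possible size.

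**1. Direct observation after zero time.** Let *d* be the days from zero time to discharge (assumed 1 to 3; not given).

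| | Counselling | Control |
|---|---|---|
| Sessions after zero time, 2 × *d* | 2, 4, 6 for *d* = 1, 2, 3 | none described |
| Breast examination and observed feeding at first contact | yes | yes |
| Scheduled calls | weeks 1, 2; months 1, 4, 6 | the same |

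The imbalance is confined to the interval from zero time to discharge. The control arm's observation of one or more feedings does not fill it, because the procedure places that observation before zero time.

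**2. Possible size.** Assume equal true risk in both arms and complete capture in the counselling arm. Let *f* be the share of in-hospital events already visible at zero time, and *r* the share of later ones recovered for controls from the record or the week-1 call. Then

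apparent RR = 1 / [*f* + (1 − *f*) × *r*].

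| | *r* = 0 | *r* = 0.5 | *r* = 0.9 | *r* = 1 |
|---|---|---|---|---|
| *f* = 0.5 | 1/0.50 = 2.00 | 1/0.75 = 1.33 | 1/0.95 = 1.05 | 1.00 |
| *f* = 0.2 | 1/0.20 = 5.00 | 1/0.60 = 1.67 | 1/0.92 = 1.09 | 1.00 |

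**3. Chance of a spurious significant excess.** Assume a true rate of 20% in both arms and *f* = 0.5. The observed control rate is then 10%, 15% or 19% for *r* = 0, 0.5 or 0.9. At two-sided 5%, the chance of a significant excess in the counselling arm is 51%, 15% or 4% with 100 women per arm, and 80%, 26% or 4% with 200 per arm. These arm sizes are also assumptions.

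Everything depends on *r*, which the document neither gives nor fixes by a procedure. The possible effect runs from none to large.

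**4. Breast outcomes.** The specific objectives compare breast complications over the first two weeks on mothers' reports, and lesions at weeks 1 and 2. Data collection instruments places the questions on lesions, pain and engorgement in calls that both arms receive. The first-contact examination uses the same instruments in both arms. Neither description of the later counselling sessions includes a repeat examination or an outcome form; only start and end times are said to be recorded. These comparisons are therefore symmetric by schedule.

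**The case against.** The strongest reply is that the article condenses a fuller protocol and that its figures are not shown, so the way adverse events are elicited and tabulated may be set out elsewhere. Control events are also not invisible: medical records are a stated source, gaps for controls may be filled from them, the registration rule covers all participants, and the week-1 and week-2 calls are identical.

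Much of this stands, and it limits the point. A reader might infer any of four stronger claims, and the documents support none of them:

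- **That control events go wholly unseen.** Records and calls can recover them. Only *direct study-team observation* is confined to one arm. On the other side, the sentences on records concern the baseline instrument and completion of the control contact; neither arranges a chart review of complications after zero time.
- **That the early breast comparisons are biased.** No passage adds findings from counselling sessions to them.
- **That discharge feeding type comes from different sources by arm and distorts the primary outcome.** The source is not stated for either arm, and the primary outcome definition does not name discharge status as a starting point. The control procedure simply describes no study contact at discharge.
- **That the direction is certain and the size known.** Recruitment and data collection procedures also excludes dyads when a researcher detects abnormal feeding mechanics or a disturbed bond. More visits could mean more such exclusions from the counselling arm, which works the other way, although the eligibility section ties this exclusion to the time of allocation.

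The missing-detail defence does not remove the core. Unequal contact is written into the plan, as is the committee's use of adverse events, and the registration rule does nothing to offset the imbalance.

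**Conclusion.** The point holds for in-hospital adverse events. From zero time to discharge, study staff directly observe only the counselling arm, and the registration rule passes that difference into data on which the committee may act. The likely direction is an inflated count in the counselling arm. The size cannot be derived: the illustrative relative risks of 1.00 to 5.00 rest on assumed values of *f* and *r*, and the false-signal figures also on an assumed event rate and arm size.

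It does not hold for complications, pain and lesions taken from the identical calls, unless sightings at counselling sessions are allowed to count. The present wording does not rule that out, so one sentence should. This is a change worth making before recruitment to the main trial, not a fatal flaw.

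**What to change.** Add to Safety protocols and Statistical analysis:

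1. Between-arm comparisons of adverse events and breast outcomes use only sources and time points applied identically in both arms: the first-contact examination, the scheduled calls and, for zero time to discharge, the medical record.
2. The medical record for that interval, including feeding type at discharge, is read with one form for every woman in both arms.
3. Events noticed only at counselling sessions are still registered, reported to the ethics committee and shown to the monitoring committee. They appear in a separate listing marked as having no equivalent observation in controls.

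The cost is one short chart extraction per woman. The downside is that events seen only at counselling sessions do not count in the comparative table; the separate listing keeps them in the committee's view. Chart entries depend on ward staff, so some events will be missed, but both arms are then read from the same source.
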